# Effects of a Parent-Child Single-Session Growth Mindset Intervention on Adolescent Depression and Anxiety Symptoms: Protocol of a 3-Arm Waitlist Randomized Controlled Trial

**DOI:** 10.2196/63220

**Published:** 2024-08-30

**Keywords:** implicit theory, fixed mindset, mental health, secondary school students, belief in change

## Abstract

**Background:**

Depression and anxiety are common mental health problems among adolescents worldwide. Extant research has found that intelligence, emotion, and failure-is-debilitating beliefs (fixed mindsets) are closely related to more depression and anxiety symptoms, hopelessness, and suicidality. Recent research also points to the importance of parental mindset, which can strongly influence children’s affect, behavior, and mental health. However, the effects of parent-child mindset interventions on a child’s internalizing problems have not yet been empirically examined. As recent evidence has shown the promise of single-session interventions in reducing and preventing youth internalizing problems, this study develops and examines a parent and child single-session intervention on mindsets of intelligence, failure, and emotion (PC-SMILE) to tackle depression and anxiety in young people.

**Objective:**

Using a 3-arm randomized controlled trial, this study will examine the effectiveness of PC-SMILE in reducing depression and anxiety symptoms among children. We hypothesize that compared to the waitlist control group, the PC-SMILE group and child single-session intervention on mindsets of intelligence, failure, and emotion (C-SMILE) group will significantly improve child depression and anxiety (primary outcome) and significantly improve secondary outcomes, including children’s academic self-efficacy, hopelessness, psychological well-being, and parent-child interactions and relationships, and the PC-SMILE is more effective than the C-SMILE.

**Methods:**

A total of 549 parent-child dyads will be recruited from 8 secondary schools and randomly assigned to either the PC-SMILE intervention group, the C-SMILE intervention group, or the no-intervention waitlist control group. The 45-minute interventions include parent-version and child-version. Both parents and students in the PC-SMILE group receive the intervention. Students in C-SMILE group receive intervention and their parents will receive intervention after all follow-up ends. Students in 3 groups will be assessed at 3 time points, baseline before intervention, 2 weeks post intervention, and 3 months post intervention, and parents will be assessed in baseline and 3-month follow-up. The intention-to-treat principle and linear-regression-based maximum likelihood multilevel models will be used for data analysis.

**Results:**

Recruitment started in September 2023. The first cohort of data collection is expected to begin in May 2024 and the second cohort will begin in September 2024. The final wave of data is expected to be collected by the end of the first quarter of 2025. The results are expected to demonstrate improved anxiety and depression among students assigned to the intervention condition, as well as the secondary outcomes compared to those in the control group. The efficacy and effectiveness of the intervention will be discussed.

**Conclusions:**

This study is the first attempt to develop a web-based single-session intervention for students and their parents to enhance their well-being in Hong Kong and beyond, which potentially contributes to providing evidence-based recommendations for the implementation of brief digital parent-child interventions.

**International Registered Report Identifier (IRRID):**

PRR1-10.2196/63220

## Introduction

### Background

Depression and anxiety are the leading causes of disability among adolescents worldwide [1]. In Hong Kong, 1 in 4 secondary school students report moderate to severe depression or anxiety symptoms [2]. Around 1 in 12 have been diagnosed with severe depression or anxiety disorders [3]. It is estimated that about 43,500 to 87,000 secondary students need support or intervention to manage their symptoms [4], but 65% of these students fail to access mental health services due to lengthy waitlists, costly clinic-based treatments, or concerns of stigmatization or discrimination [5]. Developing these disorders early in life can increase young people’s suicidal risk and lead to a wide range of psychological and vocational impairments that result in harmful long-term effects [6], especially if left untreated or given insufficient support. Thus, there is a need for integrated and effective interventions that are acceptable to families, cost-effective, and nonstigmatizing to tackle these disorders by providing early intervention and preventing deterioration.

There is substantial, robust evidence on risk and protective parenting factors for adolescent anxiety and depression [7,8]. Beyond structural elements such as academic stress [7], increasing evidence highlights the importance of parent and child belief systems, which are potentially modifiable. Mindset studies have identified that a fixed mindset (ie, believing one’s attributes are unchangeable) is a key predictor of youth mental health symptoms [9-12], while interventions promoting a growth mindset (ie, believing one’s attributes are changeable) effectively reduce adolescent depression and anxiety symptoms [13,14]. Research has also revealed that parents’ fixed mindset regarding intelligence and emotions can lead to more internalizing problems such as depression and anxiety among children and lower perceived control over mental health symptoms [15-18]. Children in fixed-mindset households might question their abilities, use ineffective coping strategies, and experience greater helplessness [9].

Research on implicit theory has found that people who believe that personal attributes can be developed (also referred to as growth mindset) are more likely to thrive in the face of difficulty and continue to improve. In contrast, those who hold a more fixed mindset may shy away from challenges or fail to meet their potential [19,20]. A growth mindset intervention’s core content teaches that people’s attributes, such as intelligence, personality, or emotions, can change and that people can improve through the actions they take (eg, making an effort, changing strategies, learning from failures, and asking for help) [19,21,22]. Emphasizing the potential to change in mindset interventions of 30 minutes to 1 hour resulted in different change effect sizes, from *d*=0.1 in changing school performance in a large-scale national study among heterogenous participants [23] to *d*=0.59 in randomized controlled trials (RCTs) on reducing anxiety [14]. Considering the brevity of the interventions and the effect sizes in relation to heterogeneity and contextual factors, low-intensity interventions on mindset have demonstrated high potential scalability for mental health prevention and early intervention measures.

Well-crafted growth mindset interventions promoting a core growth mindset are crucial to securing the effects of the intervention [19]. Existing interventions have focused on growth mindsets for intelligence [19,23], personality [14,24], and emotion [22] to promote school performance and resilience and to reduce mental health symptoms. Although these domain-specific growth mindset interventions have achieved positive improvements, there has never been an integrated intervention addressing multiple core growth mindsets. The factors for youth depression and anxiety are multifaceted, such as academic stress, failures and uncertainty in life, and the emotional struggles of puberty. Teaching multiple relevant growth mindsets in 1 intervention may address several key risk factors and strengthen the potency of growth mindset interventions to better reduce youth depression and anxiety symptoms. The proposed study will address this research gap by developing and examining an integrated intervention targeting growth mindsets for youth internalizing symptoms.

Parental mindsets matter for adolescents’ mindsets and internalizing problems such as depression and anxiety [16,17]. Parents are the most direct social support for adolescents, but parents can also be a source of stress if they hold a fixed mindset and think failure is debilitating. For example, parental fixed mindsets about intelligence predict depression symptoms and social anxiety as children have more performance worries and are afraid of negative evaluation [17]. Parents’ failure mindset also influences parenting practices in the face of setbacks [16]. A fixed emotion mindset and failure-is-debilitating beliefs in parents were associated with passive help-seeking preferences for children’s mental health symptoms [18]. In contrast, building belief-in-change about intelligence and emotion may relieve family concerns about failure, mental health symptoms, and stigmatization, increase perceived control and active help-seeking, and build better parent-child relationships. As parents play a crucial role in preventing children’s internalizing problems [25], joint parent-child growth mindset intervention is warranted and promising for promoting both parental and child well-being.

Although there is evidence of the importance of parents and children’s mindsets in internalizing symptoms, we have identified 3 important research gaps which will be tackled in the present study. First, current interventions usually focus on fixed mindsets of a single domain—such as intelligence, personality, or emotion [14,22]—but have rarely used a few relevant mindset domains in one intervention, which are closely related to youth mental health. An integrated mindset intervention is very likely to strengthen intervention efficacy, especially for brief interventions. Second, although there is an ongoing parent-child mindset intervention to promote treatment access in the United States [26], there is no such intervention in the Chinese context. In Chinese culture, parents are very anxious about their children’s education [27], and parental mindset is more likely to influence children’s mental health [28]. Third, although evidence highlights the remarkable promise of preventive parenting interventions, parenting programs are often not used even when available because of barriers such as scheduling difficulties and privacy concerns [6]. Thus, it is important to develop brief, accessible, and nonstigmatizing interventions for parents and children.

The current study will therefore develop and examine a web-based parent and child single-session intervention on mindset of intelligence, failure, and emotion (PC-SMILE). The research question is if the PC-SMILE effectively reduce depression and anxiety symptoms among secondary school students and how does it impact academic self-efficacy, psychological well-being, hopelessness, and parent-child interactions and relationships.

#### Objectives

The primary objective of this study is to evaluate the effectiveness of the PC-SMILE in reducing depression and anxiety symptoms in secondary school students (primary outcome). The secondary objective is to examine the effectiveness of the PC-SMILE in (1) enhancing academic self-efficacy, enhancing psychological well-being, and reducing hopelessness; and (2) enhancing parent-child interactions and relationships (secondary outcomes).

#### Hypotheses

This study will examine the effectiveness of the PC-SMILE for adolescents and their parents by comparing it to a child single-session intervention on mindset of intelligence, failure, and emotion (C-SMILE) intervention group that provides the child-version intervention to children only and a no-intervention waitlist control group.

Our hypotheses are the following:

H1: The PC-SMILE and C-SMILE groups have better improved primary outcome compared to the waitlist control group, including reducing anxiety and depression symptoms in student participants, while PC-SMILE is more effective than C-SMILE.

H2: The PC-SMILE and C-SMILE are more effective in the secondary outcomes of (1) reducing hopelessness, (2) enhancing academic self-efficacy, (3) enhancing psychological well-being, and (4) enhancing parent-child interactions and relationships than waitlist control, and PC-SMILE is more effective than C-SMILE.

## Methods

### PC-SMILE Intervention

Although single-session interventions (SSIs) are a relatively new intervention approach for youth mental health, rich empirical evidence has suggested the promise of SSIs for youth mental health promotion in matters such as increasing hope and happiness [29]; adaptive coping with peer stressors [30]; and improving perceived control, stress recovery, and anxiety and depression symptoms [14]. According to the literature on promoting SSI effectiveness [19,31,32] and our experience in developing SSIs in the Chinese culture [22], the PC-SMILE was designed with 5 important features to ensure efficacy.

First, the PC-SMILE addresses core beliefs related to youth depression and anxiety. The selection of intelligence, emotion, and failure mindset is based on the extant literature [17,33-36] and our fieldwork in schools based on parent and public involvement. By instilling the belief that “intelligence and negative emotions are changeable” and “failure is necessary for personal growth,” this innovative integrated intervention has a high potential to relieve parents and children’s stress and to promote well-being.

Second, the PC-SMILE was designed based on concepts and findings based on neuroscience to normalize the concepts of a growth mindset; for example, the concept of neuroplasticity is introduced to explain how and why personal traits are malleable. The core message is conveyed to participants through scientific videos and memorable metaphors. The PC-SMILE uses the muscle metaphor (ie, the brain is like a muscle, it becomes stronger and smarter when you exercise it) [19] for both students and parents, and it uses the planting metaphor for parents to emphasize the importance of patience, respect for individual differences and support for children. Illustrating ideas with metaphors is more likely to motivate sustained behavioral change [19].

Third, PC-SMILE empowers both students and their parents to act as “helpers” or “experts” by framing the participants as active contributors to the improvement of the intervention and by asking them to provide support to peers [14,32]. This design aligns with adolescents’ desire for respect [31].

Fourth, as in previous interventions [14,32], storytelling is a powerful feature of the PC-SMILE. Participants learn the stories from valued others, such as older peers and experts, which is helpful in conveying the core messages of the growth mindset. We also use the “saying-is-believing” exercise to invite the participants to share their learnings from the intervention with future intervention users. This exercise helps participants to internalize the growth mindset through cognitive dissonance processes [19,37].

Fifth, as the effects of SSIs may wane over time, booster messages will be adopted in the PC-SMILE. Weekly booster reminders [38] of core growth mindset quotations will be sent to both parent and child participants via email or text messages to sustain the mindset and behavioral changes.

### Research Design

This study will be a 3-arm cluster-RCT with a waitlist control group design. A conceptual model is provided in Figure 1. The intervention protocol will strictly follow the CONSORT (Consolidated Standards of Reporting Trials) guidelines [39,40] and has been preregistered before data collection in Open Science Framework and ClinicalTrials.gov. Classes in each eligible school will be randomized (using computer-generated random numbers) into the PC-SMILE intervention, C-SMILE, or waitlist group. The waitlist group will undergo intervention after the 3-month postintervention survey. All student participants will receive regular educational activities and interventions in school. A total of 3 repeated assessments of the measures will be conducted simultaneously for the children in three groups at (1) baseline, (2) 2-weeks post intervention, and (3) 3-months post intervention (Multimedia Appendix 1). The CONSORT flow diagram is provided in Figure 2. Cluster randomization will be conducted at the class level.

**Figure 1 figure1:**
[figure not shown]
Design of the 3-arm waitlist randomized controlled trial. C-SMILE: child single-session intervention on mindset of intelligence, failure, and emotion; PC-SMILE: parent and child single-session intervention on mindset of intelligence, failure, and emotion.

**Figure 2 figure2:**
[figure not shown]
Consolidated Standards of Reporting Trials (CONSORT) flow diagram. C-SMILE: child single-session intervention on mindset of intelligence, failure, and emotion; PC-SMILE: parent and child single-session intervention on mindset of intelligence, failure, and emotion.

### Sample Size Determination

#### Overview

We assume a small to medium effect size (Cohen *d*=0.33) of the current intervention according to a meta-analysis of SSIs addressing youth psychiatric problems [13], a power of 0.80 and an α of .05. A sample size of 438 (146 per arm) is required to detect statistical significance. With reference to the approximately 20% attrition rate of our previous studies in the school setting, 549 pairs of parent-student participants will be recruited at the baseline (183 per arm). Our existing research suggests that this is feasible within the timeframe.

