### Data Analysis

An intention-to-treat approach will be adopted. A 2-level analysis will be used to account for the cluster randomization [52]. To examine the effects of the interventions, multilevel regression will be used to test the group effect, time effect, and interaction effect on outcome measures. Additionally, we will calculate effect sizes using estimated marginal means; these effect sizes compare mean change scores (Cohen *d*), reflecting the standardized levels of change in each outcome from baseline to 2 follow-ups for youths receiving the mindset versus active control interventions. A 95% CI will be provided for each effect size. SPSS (version 26; IBM Corp) will be used for all statistical analysis.

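### The sample size of 438 is an individually randomised calculation with no design effect, so the stated 80% power at d=0.33 does not follow for a class-randomised trial

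*Protocol article*

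**What the plan says.** Under Sample Size Determination, Overview, the protocol article gives three inputs: "We assume a small to medium effect size (Cohen *d*=0.33) of the current intervention", taken from a meta-analysis, together with "a power of 0.80 and an α of .05". From these it concludes that "A sample size of 438 (146 per arm) is required to detect statistical significance". The only inflation is for loss to follow-up, introduced by "With reference to the approximately 20% attrition rate of our previous studies in the school setting", which leads to 549 dyads, 183 per arm. The section mentions no ICC, class size, design effect or baseline correlation.

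Research Design describes a different structure: "This study will be a 3-arm cluster-RCT with a waitlist control group design" and "Cluster randomization will be conducted at the class level". Participants and the Randomized Control Process gives 8 schools with 3 classes each, one class to each arm, and about 25 participating pairs (read here as per class). Data Analysis matches the design: "A 2-level analysis will be used to account for the cluster randomization".

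The Results section adds that the sample size may be changed after an effect size has been calculated from the first school.

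**The concern.** Pupils in one class share teachers, peers and the session in which they take the intervention, so their outcomes are likely to be correlated. When classes are randomised, that correlation inflates the variance of the difference between arms, and a sample size for independent individuals overstates the power. The article recognises this in its analysis but not in its sample size.

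The two-level analysis protects the type I error, so what is at stake is planning and interpretation. The stated power underlies all three contrasts in the hypotheses, including PC-SMILE against C-SMILE, which the Discussion presents as the trial's distinctive evidence. A null result set against a claimed 80% power would look like stronger evidence against an effect of 0.33 than the design may be able to give.

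**Working it through.** **1. Reproducing the stated figures.** Inputs from Sample Size Determination: d = 0.33, α = .05 (sidedness not stated), power 0.80, attrition 20%.

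- Normal approximation: n = 2(1.960 + 0.842)²/0.33² = 144.1, so 145 per arm.
- Two-sided two-sample t-test: 145.1, so 146 per arm and 3 × 146 = 438. This matches exactly; power at 146 is 80.2%.
- Attrition: 146/0.80 = 182.5, so 183 per arm and 549. This also matches exactly.
- Alternatives that do not give 146: one-sided (114 per arm), Bonferroni for two comparisons (175) or three (193), and a three-group ANOVA with f = 0.165 (357 in total).

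The inputs are used up with nothing left for a design effect. Its absence is therefore shown by the arithmetic, not inferred from silence.

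**2. Cluster structure.** 8 schools × 3 classes = 24 classes, 8 per arm. Recruited per class: 549/24 = 22.9. Analysed per class: m = 438/24 = 18.25.

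**3. Applying a design effect.** The article gives no ICC, so a range is assumed. DE = 1 + (m − 1) × ICC = 1 + 17.25 × ICC. Effective n per arm = 146/DE. Power (normal) = Φ(0.33 × √(n_eff/2) − 1.960). Detectable d = 2.802 × √(2/n_eff), where 2.802 = 1.960 + 0.842. The comparison is unadjusted, as in the article's own calculation.

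| Assumed ICC | DE | Effective n per arm | Power, normal | Power, t on 14 df | Detectable d (80%, normal) |
|---|---|---|---|---|---|
| 0 | 1.00 | 146 | 80% | 75% | 0.33 |
| 0.01 | 1.17 | 124.5 | 74% | 68% | 0.36 |
| 0.02 | 1.35 | 108.6 | 68% | 62% | 0.38 |
| 0.05 | 1.86 | 78.4 | 54% | 49% | 0.45 |

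Example at ICC 0.02: DE = 1 + 17.25 × 0.02 = 1.345; 146/1.345 = 108.6; 0.33 × √(108.6/2) = 2.431; Φ(2.431 − 1.960) = 0.68.

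The t column uses 2 × (8 − 1) = 14 cluster-level degrees of freedom. It is a separate penalty for few clusters: it already lowers power to about 75% at ICC 0 and should not be counted as part of the missing design effect. The article names no method for degrees of freedom.

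**4. Possible credit for the baseline measurement.** If the model adjusts for baseline with correlation ρ, the variance is multiplied by about (1 − ρ²), so effective n becomes 146/[DE × (1 − ρ²)]. At ICC 0.02 and an assumed ρ = 0.5: 108.6/0.75 = 144.7, power about 80% (normal). The correlation that exactly offsets the design effect is √(1 − 1/DE): about 0.38, 0.51 and 0.68 at ICC 0.01, 0.02 and 0.05.

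**5. If nobody is lost.** With all 183 per arm analysed, m = 22.9 and power (normal) is about 82%, 75% and 59% at ICC 0.01, 0.02 and 0.05.

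**The case against.** The strongest reply is that the planned analysis is more efficient than the comparison in the sample size section. Data Analysis specifies a multilevel model with group, time and interaction effects, and effect sizes based on change from baseline. With an assumed baseline correlation of 0.6, the (1 − ρ²) factor gives power of about 90% at ICC 0.01 and 86% at 0.02 (normal approximation). This stands as a possibility. A reader might infer from the missing design effect that the trial lacks 80% power, or that the power fails for any ICC above zero. The documents do not support either reading: they hold only for the unadjusted comparison of 146 per arm, and even there rounding leaves a small margin, up to an ICC of about 0.0007 by normal approximation. Equally, the article claims no baseline credit and gives no correlation, so it cannot be cited in support of the stated 80%.

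Second, the three classes are allocated within each school. If school is modelled, between-school variance drops out and only the within-school class ICC counts, so the lower end of the range may be the relevant one. This stands. The loss at 0.01 is still about six percentage points.

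Third, 24 classes is the base case. Class selection may be repeated until a school reaches 70 pairs, and more, smaller classes would reduce the design effect. The maximum likelihood models named in the Abstract also let partial responders contribute. Both points stand, but neither enters the stated calculation.

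Fourth, the Results section leaves room to adjust the sample size, so 549 is provisional. That adjustment rests on the effect size from one school. With one class per arm there, class and arm are completely confounded, so it cannot supply an ICC and does not address clustering.

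Finally, one might read the design effects as a demand for more participants. Multiplying 146 by DE gives about 172, 197 and 272 analysed per arm, but this holds class size at 18.25 and so needs more than 8 classes per arm (for example, 272/18.25 = 14.9). These are not targets for the design as described.

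**Conclusion.** The concern holds in this form: the 80% power stated for d=0.33 is that of an individually randomised trial and does not follow for the class-randomised trial the article describes. The omission itself is certain, because 146 and 183 per arm are reproduced exactly without a design effect.

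The size of the shortfall is conditional. It rests on assumed within-school class ICCs of 0.01 to 0.05, 8 classes per arm with about 18 analysed in each, and no baseline adjustment. On that basis power is about 74% to 54%, or 68% to 49% if 14 cluster-level degrees of freedom are also used. Whether the trial as it will be analysed reaches 80% cannot be settled from the article: a baseline correlation near 0.5 would about restore it at ICC 0.02 by normal approximation, while ICC 0.05 would need about 0.68.

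**What to change.** Keep the target of 549 dyads and replace the sample size sentence with a cluster calculation that states:

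- the number of classes per arm (base case 8) and the expected number analysed per class (about 18);
- a range for the within-school class ICC, with its source;
- the design effect 1 + (m − 1) × ICC;
- the reference distribution, including the cluster-level degrees of freedom if a t distribution is used;
- any credit for baseline correlation, shown as an explicit factor with the assumed correlation.

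Then restate the power at d=0.33 and the effect detectable with 80% power for 549 recruited. If the sample size is reviewed after the first school, say that this review cannot supply the ICC.

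The cost is one rewritten paragraph and, unless a justified baseline credit offsets it, a less favourable power statement. It needs no extra participants and no change to procedures.
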